| Objective(s)/
Outcome(s):                  | 
The aim of this study is to evaluate the safety of a 14 days lead-in course with Legalon® SIL (iSIL) and its effect on the hepatitis C virus load in HCV-HIV co-infected individuals who failed previous treatment with PR.
 
The specific aims are:
 
Primary aims:
 
 
• To assess the safety of iSIL in the context of HCV-HIV co-infected patients and antiretroviral treatment (ART)
 
• To evaluate the kinetics of the decline in HCV RNA from baseline to the end of a 2 weeks treatment with iSIL.
 
 
Secondary aims:
 
 
• To assess the efficacy of iSIL in a variety of clinically meaningful virological responses
 
• To evaluate drug levels of iSIL and to assess its influence on the drug-levels of co-administrated ART.
 
 
Primary endpoint:
 
 
• Frequency of adverse events during iSIL treatment.
 
• Kinetics of the decline in HCV-RNA after 2 weeks of iSIL treatment
 
 
Secondary endpoint:
 
 
• Drug levels of iSIL and its influence on the drug-level of co-administrated ART.
 
• Proportion of patients with HIV virological failure, i.e. confirmed viremia >50cp/ml.
 
 |

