#### ***Secondary endpoints:***

- Drug levels of iSIL and its influence on the drug-level of co-administrated ART.
- Proportion of patients with HIV virological failure, i.e. confirmed viremia >50cp/ml.

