## 6 STUDY DESIGN AND COURSE OF STUDY

### 6.1 General Design

This study is a multicentre, open-label, interventional study including HCV-HIV co-infected individuals with chronic HCV-genotype 1 infection and documented previous null-response (NR) or partial-response (paR) to standard therapy with SOC and progressed liver fibrosis.

The overall study-duration is 15 days. The first part is the once a day administration of iSIL from day 1 to 14. Since the half-life ( $T_{1/2}$ ) of the administrated study-drug is very short (3 hours), the follow-up of the study-subjects is one day (day 15) and the final visit will be on day 15.

Subsequent to THISTLE (at day 15) we have the intention to include the study-subjects in the SHCS trial # 688. The trial # 688 will investigate the occurrence of HCV-resistance to the HCV-PIs during TT. The duration of the # 688 will contain 48 weeks with a follow-up of 24 weeks. Importantly, we plan to review the results from the THISTLE trial with the data from the SHCS # 688.

The estimated time frame is listed below:

- Submission to ethical committee (Zurich as lead ethical committee): November 2012
- Ethical approval: January 2013
- Swissmedic approval: February 2013
- First patient enrolled: April 2013
- Enrolment: April 2013 to December 2013
- Last patient enrolled: End of December 2013

All included patients will receive a lead-in therapy with iSIL in a dosage of 20mg/kg/day for 14 days followed by standard of care TT. As mentioned above, the follow-up period will contain for one day due to short half-life time of the administrated study-drug. Moreover, a prolonged follow-up period outside THISTLE trial is warranted due to the SHCS trial # 688.

The included patients are HCV-HIV co-infected SHCS participants with chronic HCV-genotype 1 infection and documented previous null-response (NR) or partial-response (paR) to standard therapy with SOC and in urgent need of treatment (i.e. METAVIR fibrosis score  $\geq 2$  or ISHAK fibrosis score  $\geq 4$  or fibroscan stiffness  $\geq 9.5$  kPa). As cut-offs for the fibroscan we used the ones proposed in a recent review by Castera et al (17). NR is defined as less than 2 log10 IU/ml decrease in HCV RNA level from baseline at 12 weeks. paR is defined as more than 2 log10 IU/ml decrease in HCV-RNA level from baseline at 12 weeks of therapy but detectable HCV-RNA at weeks 12 and 24.

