### **9.2 Day + 1 (baseline visit), immediately previous to iSIL administration**

- Check for inclusion and exclusion criteria
- Documentation of adverse events
- Concomitant medication
- Physical examination
  - Including blood pressure while sitting (right/left), pulse rate, temperature (degree Celsius), cardiac auscultation, chest auscultation, abdominal auscultation, brief neurological examination

- Safety laboratory: full blood count, electrolytes (sodium, potassium), ASAT, ALAT, total and fractionated bilirubin, gammaGT, total protein, alkaline phosphatase, creatinine, albumin, INR
  - 10ml Heparin blood
- HCV-RNA, HIV-RNA
  - 10ml EDTA blood
- CD3/4/8 count
  - 3ml EDTA blood
- Drug level of current ART
  - 10ml EDTA blood
  - Note the time-point (date, hour, minutes) of the last intake and the dosage (milligram) on the electronic CRF
  - Blood (10 ml) must be collected in EDTA solution vacutainer tubes. The tubes containing EDTA solution should be stored at +4°C. Tubes must be identified with the patient ID number and sample number as soon as blood has been collected
  - Blood samples must be brought to the laboratories without delay (maximum 30 min after blood collection).
  - Treatment of samples: centrifugation at 1500g for 10 min at +4°C. In a class II biohazard hood plasma (obtained after centrifugation) should be divided in three labelled tubes (of approximately 1mL each) ready for freezing at -80 ° C, within one hour after collection. If this deadline cannot be met, please keep the sample at 4° C until centrifugation and freezing
- Silibinin drug-level (Cmin (T0, pre-dose), Cmax (i.e immediately after the end of silibinin infusion) and one sampling at T4 (i.e. 4 hour after the end of silibinin infusion)
  - Blood (6 ml) must be collected in ACD (acid citrate dextrose) solution vacutainer tubes. The tubes containing ACD solution should be stored at +4°C. Tubes must be identified with the patient ID number and sample number as soon as blood has been collected
  - Blood samples must be brought to the laboratories without delay (maximum 30 min after blood collection).
  - Treatment of samples: centrifugation at 1500g for 10 min at +4°C. In a class II biohazard hood plasma (obtained after centrifugation) should be divided in three labelled tubes (of approximately 1mL each) ready for freezing at -80 ° C, within one hour after collection. If this deadline cannot be met, please keep the sample at 4° C until centrifugation and freezing.

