### 9.16 Day 15 (visit 16, end of THISTLE)

- Documentation of adverse events
  - use the electronic CRF
- Concomitant medication
  - use the electronic CRF
- Physical examination
  - Including blood pressure while sitting (right/left), pulse rate, temperature (degree Celsius), cardiac auscultation, chest auscultation, abdominal auscultation, brief neurological examination
- Safety laboratory: full blood count, electrolytes (sodium, potassium), ASAT, ALAT, total and fractionated bilirubin, gamma GT, alkaline phosphatase, creatinine, albumin, total protein, INR
  - 10ml Heparin blood
- Pregnancy test:
  - 10ml Heparin blood
- HCV-RNA, HIV-RNA
  - 10ml EDTA blood
- CD3/4/8 count
  - 3ml EDTA blood
- Plasma aliquot as backup-blood for potential later analysis
  - 10ml EDTA blood
- PBMC: only at the study site Zurich
- Silibinin drug-level T24 (i.e 24 hour after the end of last silibinin infusion)
  - Blood (6 ml) must be collected in ACD (acid citrate dextrose) solution vacutainer tubes. The tubes containing ACD solution should be stored at +4°C. Tubes must be identified with the patient ID number and sample number as soon as blood has been collected
  - Blood samples must be brought to the laboratories without delay (maximum 30 min after blood collection).
  - Treatment of samples: centrifugation at 1500g for 10 min at +4°C. In a class II biohazard hood plasma (obtained after centrifugation) should be divided in three labelled tubes (of approximately 1mL each) ready for freezing at -80 ° C, within one hour after collection. If this deadline cannot be met, please keep the sample at 4° C until centrifugation and freezing.
- Accepted time window: at least one day after the end of iSIL administration

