## 10.7 Assessment of safety laboratory parameters

The laboratory tests listed in Table below will be performed at the laboratory of each study site and the laboratory of [name] in Lausanne. For time points of laboratory sampling refer to the Flow Chart. Laboratory results of the patients will be available to the investigator of each study site and selected abnormal laboratory alerts will be sent automatically to the sponsor within 24 hours. Clinically relevant laboratory values should be commented on lab report print-outs. A clinically relevant value may be either in- or outside the reference range. Out-of-range data judged as clinically significant (CS) by the Investigator has to be report as an adverse event. Clinically relevant abnormal laboratory test results must be confirmed and should be repeated until normalization or stabilization or until an alternative explanation has been found.

| Category             | Test name                                                                                                                                                                                                                                                                                                               |
|----------------------|-------------------------------------------------------------------------------------------------------------------------------------------------------------------------------------------------------------------------------------------------------------------------------------------------------------------------|
| Haematology          | Hematocrit (Hct)
Hemoglobin (Hb)
Red Blood Cell Count/ Erythrocytes
White Blood Cells / Leukocytes
Platelet Count/ Thrombocytes
Diff. Automatic Neutrophils (relative count)
Eosinophils (relative count)
Basophils (relative count)
Monocytes (relative count)
Lymphocytes (relative count) |
| Coagulation          | Prothrombin time (Quick and INR)                                                                                                                                                                                                                                                                                        |

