| Chemistry            | AST(GOT)
ALT(GPT)
Gamma GT
Albumin
Total protein
Alkaline Phosphatase (AP)
Sodium
Potassium
Glucose
Creatinine and creatinine clearance*
Bilirubin Total and fractionated                                                                                                                 |
| Lymphocyte subset    | CD3+ Lymphocyte (absolute and %)
CD4+ Lymphocyte (absolute and %)
CD8+ Lymphocyte (absolute and %)                                                                                                                                                                                                                |
| Serum Pregnancy test | Human Serum chorionic gonadotropin                                                                                                                                                                                                                                                                                      |
| Hormones             | TSH                                                                                                                                                                                                                                                                                                                     |
| HCV                  | HCV genotyping assay PCR/LIPA
Plasma HCV RNA (quantitative) with Roche
COBAS TaqMan v1.0 sensitivity range <15
UI/ml                                                                                                                                                                                           |

|            |                                                                             |
|------------|-----------------------------------------------------------------------------|
| HIV        | Plasma HIV RNA (quantitative) Roche COBAS TaqMan v2.0 sensitivity range <20 |
| Drug level | Concurrent ART drug levels
Silibinin drug level                          |

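### The HIV-failure endpoint needs confirmed viraemia, but only one HIV-RNA sample is scheduled after the first infusion and no confirmatory sample is planned

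*Protocol*

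**What the plan says.** **Endpoint.** Section 5.2 lists "Proportion of patients with HIV virological failure, i.e. confirmed viremia >50cp/ml" as a secondary endpoint, and the synopsis lists it too. Neither place says what makes viraemia *confirmed*: no number of samples, no interval and no window.

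**Sampling.** The study schedule marks HIV-RNA at screening, day 1 and day 15. The visit sections agree:
- Section 9.1 takes it at screening.
- Section 9.2, headed "Day + 1 (baseline visit), immediately previous to iSIL administration", takes it on day 1.
- Section 9.16 takes "HCV-RNA, HIV-RNA" on day 15.
- Sections 9.3 to 9.15 (days 2 to 14) list HCV-RNA only.

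**End of follow-up.** Section 6.1 says "the follow-up of the study-subjects is one day (day 15) and the final visit will be on day 15". The synopsis plans telaprevir-based triple therapy from that day.

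**Unscheduled repeats.** Section 10.7 says "Clinically relevant abnormal laboratory test results must be confirmed and should be repeated until normalization or stabilization", and its test table includes "Plasma HIV RNA (quantitative) Roche COBAS TaqMan v2.0 sensitivity range <20". Section 10.5 provides a return visit up to 30 days after treatment, for an ongoing SAE or for laboratory or vital-sign AEs past an alert limit.

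**Entry.** Section 7.2 excludes patients in need of ART for HIV virological failure only from 400 copies/ml upwards.

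**The concern.** Confirmation takes at least two values. If only one scheduled value follows the first infusion, the planned visits cannot both detect and confirm a loss of HIV control that begins under iSIL. They can, however, confirm low-level viraemia that a patient brought into the study. The endpoint then leans towards the wrong patients: by schedule, pre-existing viraemia can count and new viraemia cannot.

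Safety in co-infected patients on ART is a primary aim, and this is the only HIV virological endpoint. A low or zero count could be read as evidence that iSIL leaves HIV control intact when the planned samples were not able to test that. If analysts respond by dropping the confirmation requirement, isolated day-15 blips would be reported as failures.

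**Working it through.** The protocol gives no HIV-failure rate, alpha or power, and the analysis is descriptive (section 12.1). There is therefore no stated figure to reproduce for this endpoint. The check is a count of scheduled samples.

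**Step 1: scheduled HIV-RNA samples** (study schedule; sections 9.1, 9.2, 9.16)

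| Sample | Day | Relative to first infusion |
|---|---|---|
| Screening | -14 | before |
| Baseline | 1, pre-dose | before |
| Final visit | 15 | after |

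**Step 2: pairs that could confirm each other.** Three samples give 3 × 2 / 2 = 3 pairs.

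| Pair | Both after first infusion? | What two values above 50 cp/ml would show |
|---|---|---|
| Screening + day 1 | no | viraemia before iSIL |
| Screening + day 15 | no | first value predates iSIL |
| Day 1 + day 15 | no | viraemia already present on day 1 |

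Scheduled pairs that show onset after day 1 plus confirmation: 0 of 3.

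**Step 3: who can meet the endpoint on schedule.** Because exclusion starts at 400 copies/ml, a patient may enter with 51-399 cp/ml. If that level persists, two or three scheduled values exceed 50 and the patient can count as a confirmed failure. A patient at or below 50 at screening and on day 1, and above 50 on day 15, has one qualifying value and cannot count without a repeat.

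**Step 4: what a scheduled-only count would hide.** Suppose the true proportion with new viraemia on day 15 is p. The values of p are assumptions, and n = 20 comes from section 12.4. The expected number is 20p, and the chance of at least one is 1 − (1 − p)^20.

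| p (assumed) | Expected patients | Chance of at least one | New confirmed failures from scheduled samples alone |
|---|---|---|---|
| 5% | 1 | 64% | 0 |
| 10% | 2 | 88% | 0 |
| 15% | 3 | 96% | 0 |

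An observed 0/20 has an exact (Clopper-Pearson) 95% interval of 0 to 16.8%. That interval reflects sampling error only. It makes no allowance for events that were never open to confirmation.

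**Step 5: if confirmation were dropped.** Assume a blip rate above 50 cp/ml of 3% to 10% per sample. The protocol gives no such rate.

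| Blip rate (assumed) | Expected false failures in 20 | Chance of at least one |
|---|---|---|
| 3% | 0.6 | 1 − 0.97^20 = 46% |
| 5% | 1.0 | 1 − 0.95^20 = 64% |
| 10% | 2.0 | 1 − 0.90^20 = 88% |

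**Step 6: effect of one added sample.** With HIV-RNA also run on day 12, one pair (day 12 + day 15) lies wholly after the first infusion. Onset between day 1 and day 12 can then be confirmed on schedule. Onset after day 12 still cannot.

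**The case against.** The strongest reply is that confirmation need not come from a scheduled visit. Section 10.7 requires clinically relevant abnormal results to be confirmed and lists HIV-RNA among its tests. Section 10.2 asks for treatment-related abnormal findings to be followed until they resolve or stabilise. Section 10.5 offers a visit within 30 days of treatment. Section 9.17 stores plasma from the treatment period, and section 6.1 intends further follow-up in SHCS trial #688. A reader might infer from the schedule that no failure starting under iSIL could ever be counted, or that the rate is zero by construction. The documents do not support that, because these routes leave an ad hoc confirmation possible.

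The routes do not secure the endpoint, however:
- Section 10.7 turns on the investigator's view of clinical relevance, names no HIV-RNA threshold and sets no window. A value just above 50 cp/ml may be repeated at one of the seven centres and not at another.
- Section 10.5 depends on an SAE or an alert limit, and the protocol gives no alert limit for HIV-RNA. Under section 10.2 an abnormal result becomes an AE only with symptoms, further work-up or intervention, or a change in dosing or participation.
- Any repeat after day 15 falls after triple therapy is due to start. Section 4.1 itself warns of drug interactions and toxicity with the HCV protease inhibitors in co-infected patients.
- No HIV-RNA test is planned on the stored plasma, and its storage depends on separate consent. Trial #688 concerns HCV resistance, and no HIV confirmation is tied to it.

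A reader might also take this endpoint for the trial's only check on HIV control. It is not: ART drug levels are taken on days 1 and 12, CD4 counts on days 1 and 15, and the day-15 HIV-RNA value can itself be reported.

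Two further objections carry weight. The endpoint is secondary and descriptive, with no decision attached, which limits the severity. An SAP that is not shown may define *confirmed*, but it cannot create a sample that the protocol's visit schedule does not take.

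**Conclusion.** The point holds at moderate severity. One HIV-RNA sample is scheduled after the first infusion, and 0 of the 3 scheduled pairs can show onset under iSIL together with confirmation. Persistent entry viraemia of 51-399 cp/ml can be confirmed on schedule. New failures enter the count only through an unscheduled repeat that is discretionary, has no window for this endpoint and is open to the influence of triple therapy. Neither primary endpoint is affected.

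The count of samples and pairs needs no assumption beyond reading *confirmed* as at least two values above 50 cp/ml. The rates of 5% to 15% for new viraemia are illustrative. The blip figures (0.6 to 2.0 expected, 46% to 88% chance of at least one in 20) rest on the assumed 3% to 10% and apply only if confirmation is dropped, which the protocol does not propose.

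**What to change.** Amend section 5.2, the synopsis, the study schedule and section 9.13 as follows:

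1. Add HIV-RNA to the day-12 EDTA sample already drawn for HCV-RNA. At screening, day 1 and day 15 a single 10 ml EDTA entry already serves both assays.
2. Define confirmed on-treatment viraemia as above 50 cp/ml on both day 12 and day 15, among patients at or below 50 cp/ml on day 1.
3. Report patients already above 50 cp/ml on day 1 separately.
4. Report single day-15 values above 50 cp/ml as unconfirmed. Give the next available HIV-RNA beside each, with the caveat that it may have been taken under triple therapy.
5. State that onset after day 12 cannot be confirmed within the study.

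Testing stored day-12 aliquots is only a fallback, because section 9.17 makes their storage depend on separate consent and some patients may have none.

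The cost is a short amendment and about 20 extra assays, with no extra visit or blood. ART drug levels are also taken on day 12, so the two results could be read together.

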## 6 STUDY DESIGN AND COURSE OF STUDY

### 6.1 General Design

This study is a multicentre, open-label, interventional study including HCV-HIV co-infected individuals with chronic HCV-genotype 1 infection and documented previous null-response (NR) or partial-response (paR) to standard therapy with SOC and progressed liver fibrosis.

The overall study-duration is 15 days. The first part is the once a day administration of iSIL from day 1 to 14. Since the half-life ( $T_{1/2}$ ) of the administrated study-drug is very short (3 hours), the follow-up of the study-subjects is one day (day 15) and the final visit will be on day 15.

Subsequent to THISTLE (at day 15) we have the intention to include the study-subjects in the SHCS trial # 688. The trial # 688 will investigate the occurrence of HCV-resistance to the HCV-PIs during TT. The duration of the # 688 will contain 48 weeks with a follow-up of 24 weeks. Importantly, we plan to review the results from the THISTLE trial with the data from the SHCS # 688.

The estimated time frame is listed below:

- Submission to ethical committee (Zurich as lead ethical committee): November 2012
- Ethical approval: January 2013
- Swissmedic approval: February 2013
- First patient enrolled: April 2013
- Enrolment: April 2013 to December 2013
- Last patient enrolled: End of December 2013

All included patients will receive a lead-in therapy with iSIL in a dosage of 20mg/kg/day for 14 days followed by standard of care TT. As mentioned above, the follow-up period will contain for one day due to short half-life time of the administrated study-drug. Moreover, a prolonged follow-up period outside THISTLE trial is warranted due to the SHCS trial # 688.

The included patients are HCV-HIV co-infected SHCS participants with chronic HCV-genotype 1 infection and documented previous null-response (NR) or partial-response (paR) to standard therapy with SOC and in urgent need of treatment (i.e. METAVIR fibrosis score  $\geq 2$  or ISHAK fibrosis score  $\geq 4$  or fibroscan stiffness  $\geq 9.5$  kPa). As cut-offs for the fibroscan we used the ones proposed in a recent review by Castera et al (17). NR is defined as less than 2 log10 IU/ml decrease in HCV RNA level from baseline at 12 weeks. paR is defined as more than 2 log10 IU/ml decrease in HCV-RNA level from baseline at 12 weeks of therapy but detectable HCV-RNA at weeks 12 and 24.

A minimum of 20 study-subjects will be included based on our calculation (see below).

Importantly, we will not randomize patients to either lead-in phase with iSIL or placebo before starting TT because of ethical considerations. On the background of the excellent tolerability of iSIL together with the urgent need of a new treatment strategy for this selected difficult to treat patient population, it is not justifiable to withhold the lead-in treatment with iSIL.

